### Hypotheses

We hypothesise that a lower maternal vitamin B_12_, higher folate, higher homocysteine nutrient pattern during pregnancy adversely impacts development of brain regions. This will be reflected in brain imaging as reduced brain volume as measured through anatomical images, weaker connections in structural/functional networks (hippocampal and frontal-subcortical connections) involved in cognitive processing (memory, executive functions) as measured through DTI and rsfMRI, respectively. These structural and functional changes will in turn result in poorer neurodevelopmental outcomes (lower neuropsychological test performance, adverse temperamental traits and higher risk for common mental disorders) in the young adult offspring.’

## Methods and analysis

### Study setting

#### Pune Maternal Nutrition Study

The PMNS is a preconceptional cohort, established in six villages of Pune district, Maharashtra state, India in 1993 in collaboration with [name] and [name] and is considered a unique resource in the world to examine the DOHaD paradigm. Initially, 2466 women (F0 generation) in the reproductive age group participated in the study. A total of 814 women who became pregnant in the period June 1994 to April 1996 were enrolled for the study. Of these 797 pregnancies (with singleton pregnancy and period of gestation less than 21 weeks) were included. A total of 762 live births occurred (F1 generation). This cohort has data on preconceptional parental size, maternal nutrition and size at birth of the offspring. Maternal micronutrients vitamin B_12_, red cell folate and ferritin have been measured from blood samples collected at 18 and 28 weeks of gestation. Vitamin B_12_ levels were measured using the microbiological assay technique and red cell folate and ferritin by radioimmunoassay.^24 31^ Children are being regularly followed up for growth and development (body size and DXA body composition), nutrition and cardiometabolic risk factors (6, 12 and 18 years of age). Biological samples have been collected and stored in a biorepository and are available for assessments. The other strengths of this cohort are good community participation and follow-up rates of over 90% over the years. At 18 years follow-up, 690 of the original 762 live births in the cohort were followed up.

The participants (F1 generation) of the cohort are also part of a randomised controlled trial (Pune Rural Intervention in Young Adolescents, PRIYA)^32^ to examine intergenerational effects of micronutrient supplementation on various health outcomes. In 2012 at the age of 17 years 557 eligible members were randomised as part of the nutrition intervention trial into 1 of three groups (1) 2 micrograms/day of vitamin B_12_, (2) 2 μg/day of vitamin B_12_ with UNIMAPP multivitamins and 20 g milk powder and (3) placebo. The trial was completed in the boys in December 2017 and in the girls in September 2019. The effects of later life intervention will be adjusted during statistical analysis (figure 1—depicts time line of measurements in the PMNS cohort).

**Figure 1 F1:**
[figure not shown]
Understanding neurocognitive development using a life course approach in the PMNS. PMNS, Pune Maternal Nutrition Study.

### Subject selection

All subjects of the PMNS cohort (n=690) will be invited for participation in the study (figure 2) subject to following inclusion criteria: (1) Maternal vitamin B_12_, folate levels measured during pregnancy (2) Serial measurements done at 6, 12 and 18 years of age. Neurocognitive assessments, temperament and mental health assessments will be performed in all consenting subjects. Brain MRI will be performed on a subset of the cohort selected based on exposure to maternal vitamin B_12_ levels at 18 weeks of gestation. Median vitamin B_12_ level at 18-week gestation was 153pM (103 175 pM being the first and fourth quartiles). Description of maternal characteristics at 18-week and 28-week gestation and offspring birth characteristics are provided in online supplemental material 1. Of the 690 participants still in follow-up, 152 subjects (78 males, 74 females) whose mothers had plasma vitamin B_12_ concentration <103 pM and 154 subjects (88 males, 66 females) whose mothers had plasma vitamin B_12_ concentration >175 pM will be eligible for participation in the brain MRI scans. One hundred participants each from these two groups (total of 200 subjects) will be randomly selected.

10.1136/bmjopen-2020-046242.supp1Supplementary data

**Figure 2 F2:**
[figure not shown]
Selection of subjects from the PMNS cohort for the study. PMNS, Pune Maternal Nutrition Study.

### Assessments

The exposures and outcome measurements are summarised in table 1.

**Table 1 T1:** Exposures and outcomes defined in the study

	Exposures	Tests	Variables measured
1.	Maternal Micronutrient status and homocysteine at 18 and 28 weeks pregnancy	Biochemical assays	Vitamin B_12_, red cell folate, homocysteine

	Outcomes	Tests	Variables measured
1.	Neurocognitive performance	WAIS-IV WMS AVLT Colour Trails test	Verbal comprehension, perceptual reasoning, working memory, processing speed, Full scale IQ. Immediate memory, delayed memory and working memory. Errors in immediate and delayed recall time taken and errors for colour trails test A and B.
2.	Temperament	Adult Temperament Questionnaire	Negative affect, extraversion, orienting sensitivity, effortful control
3.	Common mental disorders	Brief Symptom Inventory Mini Neuropsychiatric Interview 7.0 for DSM 5 diagnosis	Global severity index DSM 5 diagnosis of past or current major depressive disorder, suicidality, panic disorder, agoraphobia, social anxiety disorder, generalised anxiety disorder
5.	Brain Imaging	Structural T1 MPRAGE Resting state fMRI Diffusion tensor imaging	Cortical volume and thickness Resting state functional connectivity tractography, FA and MD values in relevant white matter tracts
	Life course variables		
	Birth		Birth weight, length, head circumference, sum of skin folds
	Later life growth and development		Height, BMI, head circumference sum of skin folds at 6, 12, 18 years
	Later life nutrition		Haemoglobin, vitamin B_12_, folate, homocysteine, ferritin, glucose, lipids at 6,12,18 years
	Socioenvironmental		Mothers education, fathers education, standard of living index, adverse childhood experiences.

AVLT, auditory verbal learning test; BMI, body mass index; DSM, Diagnositic and Statistical Manual of Mental Disorders; FA, fractional anisotropy; fMRI, functional MRI; MD, mean diffusivity; WAIS-IV, Wechsler’s Adult Intelligence Scale IV; WMS, Wechsler Memory Scale.

#### Behavioural assessments

These include (1) Standardised neurocognitive test batteries—Wechsler’s Adult Intelligence Scale-IV, Wechsler Memory Scale, Auditory Verbal Learning Test, Colour Trail Test, (2) Adult Temperament Questionnaire, (3) Mental health assessments-Brief Symptom Inventory, Mini Neuropsychiatric Interview (plus 7.0). Further details of behavioural assessments are provided in online supplemental material 2 and (4) Early life stress-WHO ACE International Questionnaire (ACE-IQ).

### MRI

Anatomical data using structural 3 dimensional (3D) T1-weighted MPRAGE (magnetisation prepared rapid gradient echo) sequence, rsfMRI with 2D gradient-echo EPI (echo planar imaging) sequence and DTI using readout segmentation of long variable echo-trains (RESOLVE) sequence will be acquired on a 3 Tesla Siemens Skyra scanner.

### Image acquisition

For structural imaging, 3D T1-weighted MPRAGE images will be acquired (TR=2300 ms, TE=2.26 ms, TI=900 ms, Flip angle=8 °, slice thickness=1 mm, in-plane resolution=1×1 mm^2^, GRAPPA parallel imaging with acceleration factor of, 192 slices, FOV readout=256 mm, FOV phase encoding=100%, and acquisition time of 5 min and 21 s).

For functional imaging, T2*-weighted echo-planar imaging sequence will be used to acquire BOLD fMRI data while participants are resting with eyes open and fixated, and not thinking about anything specific. A rsfMRI scan helps to characterise brain-wide networks from a single scan as opposed to task-based fMRI which characterises evoked responses in specific brain systems. Thirty-six axial slices will be acquired covering the whole brain with a slice thickness of 3 mm, in-plane resolution of 3×3 mm^2^, TR=2000 ms; TE=30 ms; flip angle=90^0^, FOV readout=256 mm, FOV phase encoding=100%, GRAPPA parallel imaging with acceleration factor of, and 300 measurements with an acquisition time of 10 min and 8 s. Prospective acquisition correction (PACE) motion correction will be employed in this sequence.^33 34^

Diffusion-weighted images will be acquired using the RESOLVE sequence given its robustness against susceptibility artefacts. Scan parameters for RESOLVE will be: Thirty-six axial slices covering the whole brain with a slice thickness of 3 mm, in-plane resolution of 1.4×1.4 mm^2^, TR=5460 ms; TE=73/109 ms; flip angle=180°, FOV readout=220 mm, FOV phase encoding=100%, GRAPPA parallel imaging with acceleration factor of 2, 30 diffusion directions, two diffusion weightings (b values) of 0 and 1000 s/mm^2^ and an acquisition time of 14 min and 19 s.

All MRI images will be visually inspected for quality assessment and reviewed by a radiologist to rule out any structural abnormalities.

### Data management

Data will be stored at the Diabetes Unit, KEM Hospital Research Center, Pune, India. Data collected will be first entered in a paper clinical record form and double entered into an open clinical platform on a computer. Data will be downloaded and checked for extreme or missing values. Data on maternal micronutrient status during the pregnancy (nutrition intake, circulating micronutrients) and intermediate variables (birth size, childhood nutrition, growth and development, metabolic factors (insulin resistance, glycaemic status, adiposity), sociodemographic variables and socioeconomic status have been assessed previously on the cohort. These will be extracted and used for analysis.

### Statistical methods

#### Power estimation

There are 690 members of the cohort available for assessments. Assuming a 80% participation rate (from experience of previous studies on the cohort and accounting for migration) we estimate that 550 subjects would be recruited for the study. Using a test at 5% significance level, the study will have 80% power to detect an association of 0.11 SD of continuous outcome (eg, neurocognitive test score) per SD of continuous exposure (eg, maternal vitamin B_12_ level). Study of 200 subjects (100 in each group) for brain imaging will have 80% power for an effect size 0.3 and significance at p<0.05 for detecting difference between the two maternal vitamin B_12_ exposure groups.

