#### Current status and impact of COVID-19 pandemic

The study protocol was approved for funding in 2017. Subject recruitment was initiated in May 2018 and had to be halted in March 2020 due to the COVID-19 pandemic. As of March 2020, neurocognitive assessments have been performed on 386 participants of the cohort out of intended 550 participants and brain MRI scans obtained on 195 participants our of intended 200. We will try to recruit more participants once the situation is conducive. We acknowledge that due to the COVID-19 pandemic there will be some reduction in the power of the study. The results will be reported as per emerging guidelines on reporting clinical studies affected by the COVID-19 pandemic.^35^

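### Cohort power statement: on a two-sided 5% test, 550 subjects give about 73% power for 0.11 SD per SD, not 80%; the slope detectable with 80% power is 0.12

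*Protocol article*

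**What the plan says.** The Power estimation section starts from the whole cohort in follow-up: "There are 690 members of the cohort available for assessments". It applies an 80% participation rate, attributed to earlier experience with the cohort and to migration, and concludes: "we estimate that 550 subjects would be recruited for the study". The power claim follows. The test is described only as "Using a test at 5% significance level", and the claim is that "the study will have 80% power to detect an association of 0.11 SD of continuous outcome" for each SD of a continuous exposure, with maternal vitamin B12 as the example. The section gives no sidedness and no allowance for covariates.

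The section on current status and the COVID-19 pandemic reports that, by March 2020, "neurocognitive assessments have been performed on 386 participants of the cohort out of intended 550 participants". It accepts that power will fall, gives no figure, and says that recruitment may resume.

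**The concern.** This is the only power statement for the neurocognitive part of the primary objectives. With outcome and exposure both in SD units and no covariates, the slope is a correlation, so the claim can be checked from three printed numbers: 550, 0.11 and 5%. On the usual two-sided reading they do not give 80%.

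At stake is how a null result is read. Someone who takes the section at face value would put the chance of missing a true slope of 0.11 at 20%, when at full planned recruitment it is about 27%. The reduction conceded for the pandemic would also be counted from too high a starting point.

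**Working it through.** **Inputs.** From Power estimation: n = 550, slope 0.11, significance level 5%, claimed power 80%, cohort 690. From the COVID-19 section: n = 386. Assumptions: two-sided test, no covariate gain. Normal quantiles: 1.960 (two-sided 5%), 1.645 (one-sided 5%), 0.842 (80% power).

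**Planned number.** 0.80 × 690 = 552, printed as 550. This reproduces.

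**Formulas (Fisher z).**
- Power = Φ(atanh(r) × √(n − 3) − z), where z is the critical value
- Detectable slope at 80% power = tanh((z + 0.842) / √(n − 3))
- Subjects needed = ((z + 0.842) / atanh(r))² + 3

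**The stated claim, two-sided, n = 550.**
- Power for 0.11: atanh(0.11) = 0.1104 and √547 = 23.39, so 0.1104 × 23.39 − 1.960 = 0.62 and Φ(0.62) = 73.3%. Wald formulas and the exact noncentral t give 73.2% to 73.8%.
- Detectable slope: tanh(2.802 / 23.39) = 0.119. At 0.12, power is 80.5%.
- Subjects needed for 0.11: (2.802 / 0.1104)² + 3, about 646 (641 to 649 across formulas).
- Rounding: true values from 0.105 to 0.115 would all print as 0.11. They give 69% to 77%, so none reaches 80%.

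**What would yield the printed 0.11.**
- One-sided 5%, n = 550: tanh(2.486 / 23.39) = 0.106, which rounds to 0.11. Power for exactly 0.11 is 82.6%.
- Two-sided, n = 690: tanh(2.802 / √687) = 0.1065, which also rounds to 0.11. Power for exactly 0.11 is 82.5%.
- Two-sided, n = 550, with covariates unrelated to the exposure: the share of outcome variance they must explain is 1 − 550 × 0.11² / 2.802² = 1 − 6.655 / 7.849 = 0.15.

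**If recruitment ends at 386.**

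| Test | Power for 0.11 | Slope detectable at 80% power |
|---|---|---|
| Two-sided 5% | 58.0% | 0.142 |
| One-sided 5% | 69.7% | 0.126 |

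**The case against.** **Sidedness.** The strongest defence is that the section never says two-sided. A one-sided 5% test on 550 subjects has a detectable slope that rounds to the printed value, and the Hypotheses section is directional. It would therefore go too far to say that the figure is wrong under every reading. But nothing in the article declares a one-sided test. The objectives and analysis plan speak of associations and differences without a direction. For folate a single direction would be hard to defend: the hypothesis places the harm in a pattern that includes higher folate, while the Introduction cites cohorts in which poor folate status went with worse outcomes. If one-sided testing was meant, the section must still say so.

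**Covariates.** The models are to be adjusted, and adjustment can gain precision. That is fair, but the gain needed is about 15% of outcome variance from covariates unrelated to the exposure, and the power statement assumes nothing of the kind.

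**386 participants.** A reader might take the 58% as a second error. It is not: the article discloses the shortfall, acknowledges lost power and hopes to resume. The figure only puts a size on that loss.

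**Eligibility.** A reader might also infer that 550 overlooks the entry criteria, since 80% is applied to all 690 and the outer B12 groups (152 and 154) are each about 22% of 690 rather than a quarter. The article does not support that. It gives no count meeting the criteria, and the selection figure and supplement are not shown. The cut-points may come from the wider set of pregnancies, and a 28-week sample might satisfy the maternal-measurement criterion. Nor is the criterion "2) Serial measurements done at 6, 12 and 18 years of age" shown to be unnecessary: the primary objectives, Table 1 and the Objective 1 analysis use life-course data from those ages.

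**Weight.** Every available cohort member is invited, so this calculation did not set the sample size. That limits the consequence to interpretation, but it does not make the printed figure right.

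**Conclusion.** The point holds conditionally. On a two-sided 5% test with no covariate gain, the stated 80% is about 7 percentage points too high: 550 subjects give 73% power for 0.11, and 80% power is reached at 0.12. Neither the choice of formula nor rounding of the effect changes this. The conclusion rests on the two-sided convention and on an unadjusted slope. The alternatives that would recover 0.11 are an undeclared one-sided test, the undiscounted 690, or an unstated covariate gain of about 15%. The article does not show which of these, if any, produced the figure, and the match with 690 is only suggestive. The point does not extend to the derivation of 550 from 690 or to the entry criteria.

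**What to change.** In Power estimation, state the sidedness.
- If two-sided, restate the claim as: 550 subjects give 80% power for 0.12 SD per SD (73% for 0.11).
- If one-sided, say so and justify the direction for each exposure.
- If a covariate gain was assumed, give the assumed share of outcome variance.

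In the COVID-19 section, replace the unquantified concession with a figure. On the two-sided test, if recruitment ends at 386, there is 80% power for 0.14 SD per SD and 58% for 0.11. Update it if recruitment resumes.

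The cost is a few words and a slightly less favourable detectable effect. No outcome, model, entry criterion or recruitment target changes.

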Structural brain MRI analysisVoxel-based morphometry on T1 MPRAGE anatomical images will be performed using statistical parametric mapping in Matlab. Preprocessing steps will involve coregistration, segmentation. Spatial normalisation will transform all subject data to the same stereotactic space. Grey matter images will be smoothed by convolving with an isotropic Gaussian kernel. Statistical analysis using general linear model will be used to identify regions of grey matter concentration that are significantly associated with our exposures of interest.Cortical volume, thickness and hippocampal segmentation: A surface-based morphometric technique will be employed to measure cortical volume and thickness. We will use FreeSurfer software for image analysis. Standard steps include intensity normalisation, skull stripping and removal of non-brain tissues followed by segmentation, topology correction, registration and automated parcellation. Cortical volume and thickness will be computed for 68 regions (34 in each hemisphere) using the Desikan-Kelliany Atlas. The hippocampal subfield segmentation tool in FreeSurfer will be employed to compute volumes of the various hippocampal structures as per the inbuilt atlas which defines 11 hippocampal subfield structures.Structural connectivity—diffusion tractography analysis: Diffusion-weighted images will be analysed using the ‘The Diffusion Toolbox’ software tool in the FMRIB Software Library (FSL; http://www.fmrib.ox.ac.uk/fsl/fdt/index.html). After preprocessing including motion correction and eddy current correction, the DTI indices fractional anisotropy, mean diffusivity (MD) and radial diffusivity will be computed. Structural connectome generation will be performed on the MRItrix3 software. Preprocessing steps will involve denoising and correction for eddy currents. The b0 volume of preprocessed images will be extracted and registered to the T1 image using FSL’s BET tool. The fibre orientation dispersion functions (FODs) will be generated for white matter and normalised. Probabilistic streamlines tractography will be performed by dynamically seeding the normalised white matter FOD’s. The whole brain tractogram thus generated will be used for structural connectome generation.Functional connectivity: CONN software (https://web.conn-toolbox.org/) will be used for the analysis of rsfMRI data. This will involve standard preprocessing steps such as realignment, normalisation to MNI space, elimination of temporal linear trends and regressing out nuisance covariates such as residual motion and physiological artefacts. aCompCor will be used for minimising physiological artefacts. Motion censoring and interpolation will also be used to remove the effects of large frame wise displacements due to head motion. Following preprocessing, mean time series will be extracted from 91 cortical and 15 subcortical regions in the FSL Harvard-Oxford atlas, as well as from 26 cerebellar regions in the AAL atlas. These time series will be used in a whole brain functional connectivity analysis employing Pearson’s correlation coefficient between the mean time series.

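### The imaging power statement is wrong: 100 per group gives about 56% power, not 80%, for an effect size of 0.3

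*Protocol article*

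**What the plan says.** All statements are in the protocol article.

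- **Power estimation** states, of a sample of 200: "100 in each group) for brain imaging will have 80% power for an effect size 0.3", with "significance at p<0.05 for detecting difference between the two maternal vitamin B_12_ exposure groups". It does not name the effect-size metric, the sidedness of the test, or any variance explained by covariates.
- **Subject selection** confirms two independent groups, defined by maternal vitamin B12 below 103 pM and above 175 pM at 18 weeks: "One hundred participants each from these two groups (total of 200 subjects) will be randomly selected".
- **Current status and impact of COVID-19 pandemic** reports "brain MRI scans obtained on 195 participants" out of the 200 intended, and accepts some loss of power because of the pandemic.
- **Plan of data analysis, Objective 2** compares the two groups by analysis of covariance, with age, gender, total intracranial volume and adverse childhood experiences regressed out. On the number of outcomes: "Cortical volume and thickness will be computed for 68 regions (34 in each hemisphere". Hippocampal subfields, diffusion measures and functional connectivity are further outcomes. Connectivity is followed up only between regions that are significant on the structural tests.

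**The concern.** A two-group comparison with 100 per group is conventionally linked with a detectable standardised difference of about 0.4 at 80% power, so 0.3 looked too small. Group size, significance level, power and effect size are all printed, so the claim can be checked directly.

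The stake is how a null result is read. A reader who accepts 80% power for 0.3 will take a non-significant difference as fair evidence against an effect of that size. If the power is nearer 55%, such a result is almost as likely as not even when the effect is real. Because structural significance decides which regions go on to the connectivity analyses, a missed structural difference also closes off the later steps. The article says the study's results on maternal B12 will inform public health action.

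**Working it through.** **Inputs**
- n = 100 per group, two independent groups (Power estimation; Subject selection).
- Effect size 0.3 (Power estimation). The metric is not named; it is read first as a standardised mean difference d, because the stated aim is a difference between two groups.
- Significance level 0.05 (Power estimation). Two-sided is assumed first, then one-sided.
- 195 scans obtained (Current status). An even split, 97.5 per group, is assumed.

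**Trying to reproduce the stated 80%**

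Normal approximation: power = Φ(d / √(2/n) − z), with z = 1.96 for a two-sided 5% test.

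0.3 / √(2/100) = 0.3 / 0.1414 = 2.121, and 2.121 − 1.960 = 0.161, so power = Φ(0.161) = 56.4%.

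The noncentral t calculation gives 56.0%. The stated 80% is not reproduced.

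**Working backwards**
- Detectable difference at 80% power: d = (1.960 + 0.842) × √(2/100) = 2.802 × 0.1414 = 0.396. The noncentral t gives 0.398, that is 0.40.
- Sample needed for d = 0.3: n = 2 × 2.802² / 0.3² = 174.4, so 175 per group. The noncentral t gives 175.4, so 176 per group.
- Subject selection lists 152 and 154 eligible participants. Scanning all of them would give 74%.

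**Other readings (noncentral t or F unless noted)**

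| Reading | Power with 100 per group |
|---|---|
| d = 0.3, two-sided 5% | 56.0% |
| d = 0.3, one-sided 5% | 68.1% (detectable d 0.35) |
| Cohen's f = 0.3 (d = 0.6) | 98.8% |
| Correlation r = 0.3, N = 200 (Fisher z) | 99.1% |
| f² = 0.3 | >99.9% |

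None is near 80%. The stated power fits d = 0.40, or equivalently f = 0.20.

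**Covariate adjustment**

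If covariates explain a share R² of the outcome variance, the effective difference is 0.3 / √(1 − R²). For a two-sided test:

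| R² | Power at d = 0.3 |
|---|---|
| 0 | 56.0% |
| 0.2 | 65.6% |
| 0.3 | 71.3% |
| 0.4 | 77.8% |

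80% requires R² = 1 − (0.3/0.398)² = 0.43.

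**Effect of the missing scans**

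With 97.5 per group, power at d = 0.3 is 54.9% and the detectable d is 0.403. The five missing scans cost about one percentage point; the shortfall at full enrolment is 80 − 56 = 24 points.

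**Illustration for many regions**

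The article fixes no multiplicity correction. If 0.05 were divided over the 68 regions (0.05/68 = 0.00074), power at d = 0.3 would be 9.9% and the detectable d would be 0.61.

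**The case against.** The strongest reply is that the sentence is under-specified rather than wrong, because two sets of added assumptions do bring it close to 80%.

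- **Cohen's f with correction.** The planned test is an analysis of covariance, for which f is a usual metric. Taking f = 0.3 and a significance level of 0.05/68 gives 79.0%. But the section prints plain p<0.05 and mentions no correction, so this reading replaces a stated input.
- **One-sided test with covariates.** The hypotheses are directional (smaller volumes, weaker connections) and covariates are planned. A one-sided 5% test with R² = 0.28 gives 80.1%. This stands to the extent that 43% explained variance is not the only route to 80%; it is the two-sided requirement. Neither a one-sided test nor any R² is stated, and the sentence covers all brain imaging, not just volumes, for which intracranial volume might be expected to explain most.

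Three further points have some force. The 68-region figures rest on a correction the article does not adopt, and the inference plan begins with voxel-wise tests, so they are illustration only. Nothing in the article says a null result will be taken to exclude 0.3; over-reading is a risk inferred from the wrong figure. Correlations of the exposures with MRI outcomes are also planned, so the group contrast is not the only analysis.

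The admission of reduced power does not answer the point: it blames the pandemic, which explains about one of the 24 points.

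**Conclusion.** The concern holds. From the inputs printed in the section, the imaging comparison has about 56% power for 0.3 at full enrolment and about 55% with the 195 scans obtained. The difference detectable with 80% power is about 0.40 in either case. The type II error at 0.3 is about 44%, more than double the implied 20%.

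These figures assume a standardised mean difference, a two-sided 5% test, one outcome, no variance reduction from covariates and, for 195 scans, an even split. The broader conclusion, that 80% does not follow from the stated inputs, does not depend on choosing d or two-sidedness: one-sided d, f, f² and r at p<0.05 also miss it. It could be rescued only by assumptions that the section does not contain. The result does not rest on the 68-region illustration.

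**What to change.** Replace the imaging sentence in Power estimation with wording such as: *With 100 participants per group (195 scanned so far), a two-sided 5% test has 80% power to detect a standardised mean difference of 0.40 on a single outcome; power for a difference of 0.3 is about 55%.* A clause that the detectable difference would be about 0.6 if corrected over 68 regions is optional, and belongs there only if that correction is adopted.

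If the 80% relied on another effect-size metric, a one-sided test, a multiplicity correction or a covariate R², state that assumption and its value instead. Add that null imaging results will be interpreted from their confidence intervals, against the difference the study could detect.

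The cost is a sentence or two of wording and a less favourable figure. No scans, selection rules, outcomes or analyses change.

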
For each modality, the following statistical comparisons will be performed. We will first perform correlations between maternal vitamin B_12_ and folate exposures with brain MRI outcomes to examine for any linear relationships. We will use an analysis of covariance model to examine differences in MRI outcomes between low and high maternal vitamin B_12_ groups. Similarly, we will examine for differences between low and high maternal red cell folate groups (selected based on median value of maternal red cell folate) and for any interaction between maternal vitamin B_12_ and folate status. Variance due to subjects’ age, gender, total intracranial volume, ACEs will be regressed out of the analyses. Effects of additional factors (such as current vitamin B_12_ status of offspring, education status, socioeconomic status) will be examined.

For making inferences from multimodal imaging data, we will adopt a hierarchical approach. Accordingly, we will perform voxel-wise tests for difference in grey matter volume (or cortical thickness). For brain regions which are significant, DTI-based structural connectivity and fMRI-based functional connectivity between those regions will be investigated. This strategy assures that the effects of interest have both structural and functional aetiologies, and hence are likely to be robust and reproducible.

#### Objective 3

This examines causality of association between maternal nutritional factors and neurocognitive outcomes. The genetic determinants of vitamin B_12_ have been described in our population using GWAS,^36^ which will be used to calculate a gene risk score of vitamin B_12_ deficiency. Mendelian randomisation analysis (triangulation and instrumental variable analysis) using the genetic risk score for vitamin B_12_ deficiency and homocysteine (MTHFRrs1801133) will be performed.

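### The imaging power statement describes one two-group test and makes no allowance for the voxel-wise and 68-region search; read as a standardised difference, 0.3 has 56% power in one test, not 80%

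*Protocol article*

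**What the plan says.** The Power estimation section makes one claim for imaging. It begins "Study of 200 subjects (100 in each group) for brain imaging" and continues "will have 80% power for an effect size 0.3 and significance at p<0.05 for detecting difference between the two maternal vitamin B_12_ exposure groups". It names no imaging outcome, gives no SD, does not say what kind of effect size 0.3 is or whether the test is two-sided, and mentions no number of tests.

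The Plan of data analysis, Objective 2, describes a broader inference. On the surface-based measures: "Cortical volume and thickness will be computed for 68 regions (34 in each hemisphere) using the Desikan-Kelliany Atlas". On the group contrast: "We will use an analysis of covariance model to examine differences in MRI outcomes between low and high maternal vitamin B_12_ groups", with age, gender, total intracranial volume and adverse childhood experiences regressed out. On the order of inference: "we will perform voxel-wise tests for difference in grey matter volume (or cortical thickness). For brain regions which are significant". Structural and functional connectivity is then investigated between those regions.

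**The concern.** The powered test and the planned test are different. The power sentence fits a single comparison of two means at the 5% level, but the first step of the imaging inference is a search over many locations, and its outcome decides which connections are studied. A test that holds a 5% error rate over a search needs a stricter threshold at each location, and so has less power there than a single test.

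The stated figure also has to be right for a single test before it can be compared with a search, and with 0.3 read in the usual way it is not.

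What is at stake is how the imaging results are read. If few or no regions pass a corrected threshold, the finding would be set against 80% power for an effect of 0.3, which the design does not have. With 195 of 200 scans already obtained (Current status section), sample size is no longer a practical remedy; the statement of sensitivity is.

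**Working it through.** **Inputs from the article.** 100 per group; effect size 0.3; p<0.05; stated power 80% (Power estimation). 68 cortical regions, two measures each, and voxel-wise tests as the first step (Plan of data analysis, Objective 2).

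**Assumptions.** Two-sided testing; 0.3 read as a standardised mean difference d; voxel-level thresholds of z = 4.5 to 5.0, since the article gives none.

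**Formula.** Noncentral t with df = 198 and noncentrality d × √(100/2) = d × 7.07. Power is the probability of exceeding the two-sided critical value at the chosen alpha.

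**Step 1: the stated figure.** For d = 0.3 the noncentrality is 2.12, and the critical value at alpha 0.05 is 1.972. Power is 56% (68% if one-sided), not 80%. At 100 per group, 80% power needs d = 0.398; d = 0.3 would need about 175 per group.

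**Step 2: other readings of 0.3.**

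| Reading | Power, one test at 0.05 |
|---|---|
| Cohen's f = 0.3 with two groups (d = 2f = 0.6) | 98.8% |
| Correlation r = 0.3, N = 200 | 99.1% |
| d = 0.3 with ANCOVA, covariate R² = 0.43 | 80% |

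The last row comes from 0.3/√(1 − R²) = 0.398, so R² = 1 − (0.3/0.398)² = 0.43. The article states no R².

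**Step 3: one given region in a 68-region search.** Bonferroni alpha = 0.05/68 = 0.000735, critical value 3.43.

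| d | Power, single test at 0.05 | Power at 0.05/68 | Power at 0.05/136 (volume and thickness) |
|---|---|---|---|
| 0.3 | 56% | 9.9% | 7.0% |
| 0.4 | 80% | 28% | 22% |
| 0.6 | 98.8% | 79% | 73% |

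The difference detectable with 80% power at 0.05/68 is 0.605 SD. The second row shows that the mismatch remains after the single-test arithmetic is corrected.

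Bonferroni is conservative when regions are correlated. With the critical value simulated for 68 equally correlated regions (assumed correlation 0.3 to 0.9), power at d = 0.3 is 12% to 30%.

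**Step 4: the voxel-wise step.** At z = 4.5 the equivalent t threshold (df = 198) is 4.62, and the detectable d at 80% power is 0.78; at z = 5.0 these are 5.17 and 0.85. The normal approximation, (z + 0.84) × √0.02, gives 0.76 and 0.83.

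**The case against.** Several points on the other side have force.

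- **The correction method may be in the full plan.** An article commonly leaves voxel thresholds and multiplicity methods there. This stands: the absence of a named method is not the point made here. A reader might infer that the search will be run at uncorrected p<0.05 and count the false regions that would follow. The article does not say so. Its p<0.05 is the alpha of a power calculation, and the hierarchical step says only that regions are significant.
- **The metric is undefined.** A reader might conclude that 80% power and a 5% error rate over the search can never hold together. That is too strong: if 0.3 is Cohen's f, Bonferroni over 68 regions gives 79%. That reading does not rescue the sentence, since its single test would then have 98.8% power; over both measures it gives 73%, and at an assumed voxel threshold of z = 5.0 about 19%.
- **ANCOVA raises power.** With covariates explaining 40% of variance (assumed), d = 0.3 has 78% power in one test and 25% at the 68-region level. This softens the figures without restoring 80% for the search.
- **Power for one region is not power to find any region.** With 10 regions affected at 0.3 SD (assumed) and independent tests, the chance of finding at least one is 1 − (1 − 0.099)^10, about 65%, and it is lower if they are correlated. The 10% therefore applies to a given region only.
- **The 132 functional regions do not add to the gating search.** They supply time series for the connectivity analysis; under the hierarchical approach, connectivity is examined between regions that pass the structural step.

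**Conclusion.** The concern holds in a limited form. The imaging power statement belongs to a single two-group comparison and takes no account of the search that opens the hierarchical analysis. As a standardised mean difference, 0.3 has 56% power in one unadjusted two-sided test. It reaches 80% only with a covariate R² of about 0.43, which is not stated. In a 68-region search at a family-wise 5% level, power for a given region is about 10% at 0.3 SD and 28% at 0.40 SD, with a detectable difference of about 0.6 SD.

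The voxel-wise step needs larger effects, about 0.78 to 0.85 SD at the assumed thresholds, so a region-level figure should not be carried over to it. These sizes rest on two-sided testing, 100 per group, no covariate gain and, for the regions, Bonferroni. Correlation-aware correction or useful covariates would improve them.

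**What to change.** In Power estimation:

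1. Define the effect-size metric and the sidedness of the test.
2. Restate the single-test figure as about 0.40 SD at 80% power, or 56% power at 0.3 SD, unless a covariate R² is stated and justified.
3. Say that this figure applies to one prespecified imaging contrast and not to the search. The contrast is for the investigators to choose: the Hypotheses section names reduced brain volume and hippocampal and frontal-subcortical connections, but no single imaging outcome such as total hippocampal volume.
4. State the detectable difference for the region-wise search (about 0.6 SD under Bonferroni over 68) and, separately, for the voxel-wise search at its chosen threshold.

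In Objective 2, say that only regions passing the multiplicity-corrected threshold count as significant in the hierarchical step.

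The cost is wording and standard correction options in the imaging software, with no new scans or participants. The downside is that the stated sensitivity of the imaging study becomes less favourable.
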